### Secondary outcomes measured at 1, 6 and 12 months

Risk perception: family history of colorectal and other cancers, are excluded perceived risk, both absolute and comparative, is measured using validated scales from our previously published systematic reviews and primary research on colorectal cancer risk [28, 29].Generalised anxiety using the State-Trait Anxiety Inventory (STAI) scale [30].Cancer-specific anxiety using an established measure applied extensively in cancer screening research, and previously modified for colorectal cancer [31, 32].Intentions to have an iFOBT and/or colonoscopy in the next 3 months, based on items from the Theory of Planned Behaviour and previous research [29, 33].Clinical outcomes of screening tests (e.g. detection of polyps and cancers), obtained from GP records (Additional file 3).

### Other secondary outcomes

6.Proportion of participants who have had risk-appropriate screening measured after 5 years from baseline.7.Health service utilisation and healthcare costs resulting from implementation of the CRISP tool.

### Measurement timing

Colorectal cancer screening behaviour will be collected for a maximum period of 4.5 years prior to recruitment (the maximum period for which historic Medicare Benefits Schedule data can be requested) and 5 years from recruitment. The timing, modality and results of any previous screening will be used to determine the time interval and modality of screening during the trial period to measure the appropriate screening outcome. Screening data at 1 year after recruitment will be used to determine the primary outcome.

The participant-completed outcome measures (self-reported screening behaviour, risk perception, general anxiety, cancer worry and intention to screen) are captured at baseline and 1, 6 and 12 months (Fig. 4).

**Fig. 4 Fig4:**
[figure not shown]
Schedule of enrolment, interventions and assessments. Baseline risk factors include age, sex, height, weight, smoking, medications, dietary habits and previous colorectal cancer screening

### Sample size and power calculation

Sample size calculations were initially based on previously published rates of risk-appropriate screening [11, 12] and a 6.5% prevalence of increased risk of colorectal cancer in a primary care population [35]. Based on these data, allowing for 10% attrition at 12-month follow-up, to achieve 90% power with a two-sided 5% level of significance, the sample size was calculated at 278 participants per arm to detect, at a minimum, a 10% difference in the percentage of risk-appropriate screening at 12 months between the intervention and control arms. Given the low estimated rates of risk-appropriate screening, we considered several scenarios where the risk-appropriate screening at 12 months also increased in the control arm (Table 1) and selected a more conservative sample size that was achievable and practical. Using data from the NBCSP [36] and data on the benefits and harms of colonoscopy [5, 37], an estimated 10% improvement in risk-appropriate screening would be associated with the following outcomes per 1 million people aged 50 and older: 92,000 more faecal occult blood tests, 3000 fewer colonoscopies and 55 fewer deaths.

**Table 1 Tab1:** Required samples sizes for three different scenarios of increases in risk-appropriate screening in the intervention arm compared to the control arm, assuming rate of risk-appropriate screening of 1% and 25% at baseline and level of significance = 0.05

Scenario (intervention vs control)	Absolute difference in appropriate screening	Power	Sample size per arm	Sample size per arm allowing for 10% attrition
10% improvement vs 0%	11% vs 1%	90%	117	130
10% improvement vs 2.5%	11% vs 3.5%	90%	250	278
10% improvement vs 5%	11% vs 6%	90%	652	725
10% improvement vs 0%	35% vs 25%	80%	329	366

### Revised sample size: updated using baseline data

Recruitment started in May 2017 after ethics approval was granted. In December 2017 it became clear that we were recruiting faster than anticipated and were close to reaching our initial target sample size. At the quarterly Trial Steering Committee meeting it was decided to review the sample size assumptions to ensure that the study was adequately powered. We were concerned that the percentage of individuals with risk-appropriate screening may be higher in the primary care population than had been found in previous community-based studies [11, 12] that had been conducted prior to the roll-out of the NBCSP in 2006. Based on baseline survey and self-reported colorectal cancer screening of the 397 participants collected prior to randomisation, we conservatively estimated that risk-appropriate screening of the trial population at baseline was no greater than 25%. The Trial Steering Committee reviewed these data in February 2018 and recommended to increase the sample size to 366 per arm (allowing for 10% attrition over the 12 months) to ensure that the study has at least 80% power to detect a minimum of 10% difference in the percentage of risk-appropriate screening at 12 months between the intervention and control arms, assuming that 25% of the control participants receive risk-appropriate screening at 12 months.

### Statistical methods

Baseline participant characteristics will be compared between the two study arms using descriptive statistics to assess for chance imbalance. The primary analysis will compare the proportion of participants who have had risk-appropriate colorectal cancer screening at 12 months using logistic regression with the randomisation stratification factor, general practice, as a covariate. The analysis will be repeated for the risk-appropriate colorectal cancer screening at 5 years as a secondary longer-term outcome. Comparisons between arms on continuous secondary outcomes will use a linear mixed-effects model that includes arm (intervention and control), general practice and time (baseline, 1, 6 and 12 months) as fixed effects and individuals treated as random effects, with two-way interactions between study arm and time, except baseline where study arm means will be constrained to be equal.

Comparisons between study arms on binary secondary endpoints with repeated outcomes measures will be performed using logistic regression, using generalised estimating equations with robust standard errors to allow for the repeated outcome measures on individuals, with general practice included as a covariate. All analyses will be conducted in Stata 15 [38]. The estimated intervention effects will be reported as the odds ratio for binary outcomes and the difference in means between the intervention and control arms for continuous outcomes. All estimates will be reported with respective 95% confidence intervals and *p* values. For the secondary continuous outcomes, pre-specified adjustment for baseline outcome measure will increase the precision of the estimated intervention effect and may adjust the intervention effect if there is imbalance on this measure at baseline.

A sensitivity analysis will be performed on the primary and secondary endpoints to adjust for additional pre-specified baseline variables, for example age, sex and family history of colorectal cancer, in the regression models to explore whether the estimated intervention effect is affected by the potential for imbalance of these confounders in the sample.

A sensitivity analysis will also be conducted to assess the impact of using the revised 2017 Australian Colorectal Screening guidelines on the proportion of participants classified as having risk-appropriate colorectal cancer screening at 12 months and 5 years. All randomised participants will be included in the analysis in their assigned study arms in accordance with the intention-to-treat principle [39]. Possible differential attrition will be assessed by comparing baseline characteristics of those who withdraw against those who remain in the study. Appropriate methods for dealing with missing data will be detailed in the statistical analysis plan and be informed by a blinded review of the data. Sensitivity analysis will be used to assess the robustness of the missing data assumption.

A health economic analysis will combine a within-trial and modelled analysis of the cost-effectiveness of implementing the CRISP tool. The within-trial analysis will focus on the incremental cost per appropriately screened individual for the CRISP tool versus usual care. The modelled analysis will combine observed colorectal cancer detection rates from the trial with data from the published literature to investigate the longer-term cost-effectiveness of the CRISP tool using an economic model. Within-trial costs in the two study arms will be estimated based on data observed from general practice, MBS, the NBCSP and the VAED records. Mean estimates of costs will be used and confidence intervals will be generated by resampling (boot-strap) techniques. Benefits in the modelled analysis will be assessed as quality-adjusted life years (QALYs) by extrapolating the observed cancer detection rates from the trial to longer-term survival and adjusting them by published quality of life (utility) weights. Results will be presented in terms of the incremental cost-effectiveness ratio (ICER) as a cost per case detected for the within-trial period, and a cost/QALY gained for the modelled analysis. Sensitivity analyses will be conducted to test the robustness of the results of the economic analysis to variations in the underlying assumptions and inputs.

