### Data collected

Baseline data collected include: demographics (age, sex, postcode, language spoken at home and country of birth, marital status, highest education level attained) and clinical variables (age, height, weight, number of first-degree relatives with colorectal cancer and ages of diagnoses, smoking history, current fruit and red meat consumption, history of use of non-steroidal anti-inflammatory drugs, current use of hormone replacement therapy (women only) and calcium supplements, and history and clinical outcomes of previous FOBT, colonoscopy including previous polyps) [15]. Additional baseline measures of CRC risk perception [28, 29], generalised anxiety [30], cancer worry [31, 32] and intention to screen [33] are also included in the baseline questionnaire.

Health service use is tracked using data extracted from the Australian Government Department of Health Medicare Benefits Schedule (MBS) [34] that maintains information about visits to healthcare providers and diagnostic tests, the National Bowel Cancer Screening data to access FOBT screening and the Victorian Hospital Admitted Episodes Dataset (VAED) to access privately funded colonoscopic screening.

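### The primary model adjusts only for practice and reports only an odds ratio: a possible precision gain from baseline screening status is forgone, and no risk difference is planned although the trial is sized on one

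*Protocol article*

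**What the plan says.** All references are to the Protocol article.

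- **Primary model** (Statistical methods): the proportions are compared "using logistic regression with the randomisation stratification factor, general practice, as a covariate". No other covariate is named.
- **Effect measure** (same section): "The estimated intervention effects will be reported as the odds ratio for binary outcomes", with 95% confidence intervals and p values. No risk difference is named.
- **Baseline adjustment** (same section): it is planned for continuous secondary outcomes, on the stated ground that it improves precision and can deal with imbalance. The GEE models for repeated binary secondary outcomes name general practice as the only covariate.
- **Sensitivity analysis** (same section): further baseline variables are added to the models, "for example age, sex and family history of colorectal cancer", to see whether the estimated effect changes. Previous screening is not among the examples.
- **Screening history** (Data collected): the baseline questionnaire, completed before randomisation, records "history and clinical outcomes of previous FOBT, colonoscopy including previous polyps". Measurement timing adds: "The timing, modality and results of any previous screening will be used to determine the time interval and modality of screening" against which the trial-period outcome is judged.
- **Sizing** (Revised sample size): the trial has "at least 80% power to detect a minimum of 10% difference in the percentage of risk-appropriate screening at 12 months", "assuming that 25% of the control participants receive risk-appropriate screening at 12 months". Baseline risk-appropriate screening was put at no more than 25%, from 397 participants.

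**The concern.** Previous screening is more than a generic prognostic factor here. It sets which test a participant should have and when, so it enters the scoring of the primary outcome. The protocol's own precision argument for continuous outcomes applies equally to the primary one, but is not used there. The revision also lowered the power target from the first calculation, which was "to achieve 90% power with a two-sided 5% level of significance", to 80%, so extra precision would be useful.

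The second issue is the scale. The trial is sized on an absolute difference, but the planned summary is an odds ratio, which cannot be read as percentage points without the control rate.

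The third follows from the second. The sensitivity analysis asks whether adding covariates alters the estimate. An odds ratio can change when a prognostic covariate is added even if the arms are perfectly balanced, so on that scale the check can suggest imbalance where there is none.

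**Working it through.** **1. The plan's own sample size.** Inputs (Table 1, last row, and Revised sample size): 35% v 25%, two-sided 5%, 80% power, 10% attrition.

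n per arm = [z₀.₉₇₅ √(2p̄q̄) + z₀.₈₀ √(p₁q₁ + p₂q₂)]² / (p₁ − p₂)², with p̄ = 0.30

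= [1.960 × √0.42 + 0.842 × √0.415]² / 0.10² = (1.270 + 0.542)² / 0.01 = 328.5, so 329.

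329 / 0.9 = 365.6, so 366 per arm and 732 in total. Both figures reproduce with no covariate adjustment. Power at 329 per arm is 0.801.

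**2. What adjustment could add.** The strength of association is not in the documents, so it is assumed over a range. Set-up: 329 analysed per arm, 8 practices (given no effect of their own), 25% up to date at baseline, overall success 25% v 35%, 2,000 simulated trials per scenario, Wald test at 5%. Because prevalence and control rate are both 25%, phi in the control arm equals the difference in control success between those up to date and those not. For example, 0.25 × 55% + 0.75 × 15% = 25%, with phi = 0.55 − 0.15 = 0.40.

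| Control success, up to date v not | phi | Power, practice only | Adjusted, common odds ratio | Adjusted, effect only in those not up to date |
|---|---|---|---|---|
| 25% v 25% | 0 | 0.80–0.81 | 0.80 | 0.81 |
| 40% v 20% | 0.2 | 0.80–0.81 | 0.82 | 0.80 |
| 55% v 15% | 0.4 | 0.81 | 0.87 | 0.85 |
| 70% v 10% | 0.6 | 0.80 | 0.93 | 0.91 |
| 85% v 5% | 0.8 | 0.80–0.81 | 0.99 | 0.98 |

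The Monte Carlo standard error near 0.80 is √(0.8 × 0.2 / 2000) = 0.009, so the phi 0.2 row shows little or no gain.

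**3. Size of chance imbalance.** For a 25% factor at 329 per arm, the standard error of the between-arm difference is √(2 × 0.25 × 0.75 / 329) = 3.4 points, and 1.96 standard errors is 6.6 points. An imbalance of that size moves the unadjusted difference by 6.6 × 0.40 = 2.6 points at phi 0.4, or 6.6 × 0.60 = 4.0 points at phi 0.6, against a 10-point target. This is ordinary sampling error already in the confidence interval, not bias. Adjustment would remove it.

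**4. Odds ratio against the design target.** Planned odds ratio = (0.35/0.65) / (0.25/0.75) = 1.615.

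- Control rate 10%: odds 0.1111 × 1.615 = 0.1795, so 15.2%, a difference of 5.2 points.
- Control rate 20%: 28.8%, a difference of 8.8 points.
- Control rate 40%: odds 0.6667 × 1.615 = 1.077, so 51.9%, a difference of 11.9 points.

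**5. Odds ratios across adjustment sets.** In the common-odds-ratio scenarios the overall effect is always 25% v 35%, marginal odds ratio 1.615. The odds ratio conditional on baseline status is 1.77 at phi 0.4 (55% to 68.4%; 15% to 23.9%) and 2.11 at phi 0.6 (70% to 83.1%; 10% to 19.0%). The risk difference stays at 10 points throughout.

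**The case against.** Adjusting for the stratification factor alone is a coherent, valid choice, and randomisation protects the test whatever else is left out. That stands.

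A reader might infer that the plan loses power. It does not: the sample size assumes no adjustment and the 80% is met.

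A reader might also infer that baseline status largely determines the outcome. The protocol gives no figure for this. Someone up to date at baseline may or may not fall due within 12 months, so even the direction is not certain. The free kit and its reminder go only to average-risk participants who are due, so the scenario with no effect in those up to date is a realistic one, and at phi 0.2 its gain is nil.

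Nor is the 10-point difference never estimated. The primary analysis compares proportions, and the within-trial cost per appropriately screened individual needs their difference. What is absent is a risk difference with CI as a planned reported effect.

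The sensitivity covariates are an open list, so previous screening is not excluded there, and the SAP, which is not shown, may name it. But the protocol defers missing-data methods to the SAP while stating the primary model and effect measure outright, and the point rests on those.

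The covariate is not ready-made. Appropriateness is judged by different rules in the two arms, and self-report is at the bottom of the source hierarchy. Both points affect how the variable is built; neither argues against building it. The odds-ratio shift in step 5 is for an assumed baseline screening covariate; for age, sex and family history it could be small.

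**Conclusion.** The point holds as a worthwhile improvement to a valid plan. The primary model leaves out a pre-randomisation variable that feeds into how the outcome is judged and is likely to be prognostic, although the protocol accepts the precision argument elsewhere. The gain in power depends on an association that the documents do not give: about nil to 2 points at phi 0.2, about 4 to 6 at phi 0.4, and about 11 to 13 at phi 0.6. These figures assume 25% prevalence, 25% v 35% success and 329 analysed per arm.

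The mismatch of scale needs no such assumption. The target is an absolute 10 points, the planned summary is an odds ratio, and the same odds ratio covers roughly 5 to 12 points for control rates of 10% to 40%.

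**What to change.** Before unblinding:

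1. Add baseline screening status (up to date v due) to the primary logistic model alongside practice. Derive it from the pre-randomisation questionnaire by a single written rule applied identically in both arms.
2. Report the standardised marginal risk difference with 95% CI beside the odds ratio, for instance from Stata's margins command after the logistic model.
3. Judge the covariate sensitivity analysis on the risk difference.
4. Add the baseline value to the GEE models for binary secondary outcomes where one was collected.

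The cost is an SAP paragraph and a few lines of code, with no new data and no change to the sample size. There are two small downsides. The baseline variable has to be constructed from self-report, so it carries some misclassification, which would reduce the gain. The odds ratio also becomes conditional on screening status as well as practice, so the text should say which effect is conditional and which is marginal.

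### With a participant random effect as the only stated dependence, standard errors for the continuous secondary outcomes hold only if variance and correlation are equal across the four visits

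*Protocol article*

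**What the plan says.** The Statistical methods section sets out the model term by term. The fixed part begins "Comparisons between arms on continuous secondary outcomes will use a linear mixed-effects model that includes arm (intervention and control), general practice", and the sentence goes on to "time (baseline, 1, 6 and 12 months) as fixed effects and individuals treated as random effects". Arm-by-time interactions follow, "except baseline where study arm means will be constrained to be equal". This is a constrained-baseline longitudinal model.

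No random slope, residual covariance structure or robust variance is mentioned for this model. The next paragraph, on binary repeated outcomes, does name one: logistic models "using generalised estimating equations with robust standard errors to allow for the repeated outcome measures on individuals".

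Under Measurement timing, the participant-completed measures "are captured at baseline and 1, 6 and 12 months", so the gaps between successive visits are 1, 5 and 6 months. In the Statistical methods section, only the handling of missing data is explicitly deferred to the statistical analysis plan (SAP).

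**The concern.** A random intercept with independent, constant-variance residuals implies one variance and one correlation for every pair of visits (compound symmetry). Scores for anxiety, worry and perceived risk may well correlate more strongly one month apart than twelve months apart.

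The constrained baseline adds to this. In such a model, the working covariance also sets how strongly each follow-up visit is adjusted for baseline. A single averaged correlation adjusts too little at 1 month and too much at 12 months, and the model-based SE does not show it.

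The visits are reported separately, so opposite errors at 1 and 12 months do not cancel. The second hypothesis concerns cancer-specific anxiety at all three follow-up times, and the Data monitoring section names increased cancer worry as the most likely adverse event. An SE that is too large at 1 month could hide an early rise in worry. One that is too small at 12 months would overstate the evidence for a late effect.

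**Working it through.** **1. The plan's own figure.** No SD, correlation or power is given for any continuous outcome. The only design figure available is the number per arm, from the primary outcome (35% vs 25%, 80% power, two-sided 5%):

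n = [1.960 × √(2 × 0.30 × 0.70) + 0.842 × √(0.35 × 0.65 + 0.25 × 0.75)]² / 0.10² = (1.270 + 0.542)² / 0.01 ≈ 329, and 329 / 0.9 ≈ 366.

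Both agree with Table 1. The number per arm cancels from the ratios below.

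**2. Formula.** Take complete data with n per arm. Let s_j be the true SD at visit j (s_0 at baseline) and c_j the true correlation of visit j with baseline. A fitted random intercept tends to the average variance v and to r = average covariance / v. The arm difference at visit j is the follow-up difference minus r times the baseline difference, so:

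- model variance = (2/n) × v(1 − r²)
- true variance = (2/n) × (s_j² − 2·r·c_j·s_j·s_0 + r²·s_0²)
- SE ratio = √(model / true)
- type I error = 2[1 − Φ(1.96 × ratio)]

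A ratio below 1 means that the reported SE is too small.

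**3. Worked case.** Assume constant SD = 1 and correlation 0.7 at a 1-month gap, falling geometrically to 0.5 at 12 months. The six pairs have gaps of 1, 6, 12, 5, 11 and 6 months and correlations 0.700, 0.601, 0.500, 0.619, 0.516 and 0.601. Their mean is r = 0.589, so r² = 0.347.

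- Model: 1 − 0.347 = 0.653.
- 12 months: true = 1 − 2 × 0.589 × 0.5 + 0.347 = 0.758; ratio √(0.653/0.758) = 0.928; type I error 6.9%.
- 1 month: true = 1 − 2 × 0.589 × 0.7 + 0.347 = 0.522; ratio √(0.653/0.522) = 1.118; type I error about 2.9%.

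**4. Other assumed patterns.** SDs are listed for baseline, 1, 6 and 12 months.

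| Correlation, 1- to 12-month gap | SDs | Ratio at 1 / 6 / 12 months | Type I error at 12 months |
|---|---|---|---|
| 0.6 throughout | constant | 1.000 / 1.000 / 1.000 | 5.0% |
| 0.7 to 0.6 | constant | 1.066 / 1.008 / 0.953 | 6.2% |
| 0.7 to 0.5 | constant | 1.118 / 1.010 / 0.928 | 6.9% |
| 0.8 to 0.4 | constant | 1.279 / 1.012 / 0.882 | 8.4% |
| 0.7 to 0.5 | 1, 1.05, 1.10, 1.15 | 1.142 / 0.989 / 0.876 | 8.6% |
| 0.7 to 0.5 | 1, 0.95, 0.90, 0.85 | 1.097 / 1.038 / 0.993 | 5.2% |
| 0.7 to 0.5 | 1, 0.90, 0.85, 0.80 | 1.119 / 1.054 / 1.005 | 4.9% |
| 0.6 throughout | 1, 0.95, 0.90, 0.85 | 0.977 / 1.029 / 1.084 | 3.4% |

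**5. Dependence on correlations among follow-up visits.** Hold the baseline correlations at 0.7, 0.6 and 0.5, with constant SD, and give the three follow-up pairs a common correlation f. Then r = (1.8 + 3f)/6.

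| f | r | Ratio at 12 months | Type I error |
|---|---|---|---|
| 0.50 | 0.550 | √(0.6975/0.7525) = 0.963 | 5.9% |
| 0.60 | 0.600 | √(0.6400/0.7600) = 0.918 | 7.2% |
| 0.65 | 0.625 | √(0.6094/0.7656) = 0.892 | 8.0% |
| 0.70 | 0.650 | √(0.5775/0.7725) = 0.865 | 9.0% |

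The same baseline correlations thus give a 12-month SE anywhere from 4% to 14% too small.

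**6. Unstructured covariance.** Each visit is adjusted with its own correlation, and model and true variance agree at (2/n) × s_j²(1 − c_j²). In the worked case at 12 months this is 0.750 against 0.758, an SE ratio of 0.995. Over all patterns tried, the true 12-month SE was 0–4% smaller than under the random intercept and never larger.

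**7. Dropout.** With 10% monotone dropout, the SE ratios moved by less than 0.01.

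**The case against.** The strongest reply is that the text nowhere says that the random effect is the only dependence, or that residuals are independent with constant variance. A participant random effect can be combined with heterogeneous or serially correlated residuals, or with robust SEs, and Stata 15 offers these. Residual structure is a common SAP item, the SAP is not shown, and an article may leave such detail to it.

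This stands in part: the random-intercept reading is an inference, so the point must be conditional. It does not dispose of the point. The article does state how within-person dependence is handled, and its sentence describes what Stata fits by default. The neighbouring paragraph names a robust variance for the same kind of repeated data.

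A reader might also infer more than the document supports:

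- *That the SEs are wrong for every continuous outcome.* Under compound symmetry they are exact.
- *That the 12-month SE is always too small.* The direction depends on the SDs. With a falling SD it can be about right, or up to 8% too large in the patterns listed.
- *That one figure measures the error.* No scale has a stated SD or correlation, and step 5 shows that fixing the baseline correlations alone does not determine the result.
- *That the treatment effects are biased.* A wrong covariance can bias estimates when data are missing at random. That bias was not quantified here, planned attrition is 10%, and missing-data methods are left to the SAP.

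**Conclusion.** The point holds in conditional form. If the model is fitted as the sentence plainly reads, its SEs are valid only under equal variance and equal correlation across the four visits, and no robust variance protects against departures.

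With constant SD and correlation falling from 0.7 to 0.5–0.6, the 1-month SE is about 7–12% too large and the 12-month SE about 5–7% too small. Across the wider constant-SD decay patterns, the 12-month shortfall is mostly 5–12%, with type I error about 6–8%; the extremes in step 5 are 4% and 14%. All of this rests on assumed correlations and SDs, and on a large-sample calculation that ignores the practice covariate.

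The effect is modest and confined to continuous secondary outcomes, taken here to include the anxiety and cancer worry scales. The primary logistic analysis and the sample size are untouched. It deserves correction because the remedy is nearly free and these outcomes carry the trial's question about psychological harm.

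**What to change.** Keep the mean model as written: arm-by-time effects, general practice, and a common baseline mean. Specify an unstructured residual covariance over baseline, 1, 6 and 12 months in place of the random intercept. That is 10 parameters (4 variances and 6 covariances) estimated from 732 participants. In Stata, use `mixed` with `residuals(unstructured, t(time))` and suppress the participant intercept, which an unstructured matrix makes redundant.

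Name the fallback in advance: if the model does not converge, use the random intercept with robust SEs clustered on participant. This corrects the SEs but still applies one averaged baseline adjustment to every visit.

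The cost is one sentence in the SAP, a few more covariance parameters and a small risk of non-convergence. Data collection and sample size do not change.

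### The stated model for repeated binary secondary outcomes leaves out the baseline value that is collected, which costs efficiency and consistency but not validity

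*Protocol article*

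**What the plan says.** All references are to the protocol article.

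- **Binary secondary outcomes (Statistical methods).** Repeated binary endpoints are analysed by logistic GEE with robust standard errors "to allow for the repeated outcome measures on individuals, with general practice included as a covariate". No baseline outcome, time term or arm-by-time term is mentioned.
- **Continuous secondary outcomes (same section).** Baseline is one of four time points in a linear mixed model "with two-way interactions between study arm and time, except baseline where study arm means will be constrained to be equal".
- **Reason given for using baseline (same section).** "For the secondary continuous outcomes, pre-specified adjustment for baseline outcome measure will increase the precision of the estimated intervention effect", and it "may adjust the intervention effect if there is imbalance on this measure at baseline".
- **Sensitivity analysis (same section).** Primary and secondary models are refitted to "adjust for additional pre-specified baseline variables, for example age, sex and family history of colorectal cancer".
- **What is collected (Data collected; Measurement timing).** Measures of risk perception, general anxiety, cancer worry and screening intention "are also included in the baseline questionnaire", and they are repeated at 1, 6 and 12 months.

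**The concern.** The two families of secondary outcome are treated differently without a stated reason. A baseline response usually predicts the later response to the same item. Including it sharpens the comparison and removes most of the effect of a chance difference between arms at baseline. The protocol makes this argument itself, then confines it to continuous outcomes. The measurement needed is already in hand for any binary endpoint taken from the questionnaires.

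At stake are the power of those binary comparisons and how far a single realised estimate is moved by chance imbalance. The primary outcome and the sample size are not involved.

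**Working it through.** **1. The plan's own figure.** Table 1 concerns the primary outcome, but it supplies the sample size used below. For 35% vs 25%, two-sided 5%, 80% power, with pooled variance and no continuity correction:

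n = [1.96·√(2·0.30·0.70) + 0.8416·√(0.35·0.65 + 0.25·0.75)]² / 0.10² = [1.2702 + 0.5422]² / 0.01 ≈ 328.5, so 329 per arm. With 10% attrition, 329/0.9 = 365.6, so 366.

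Both match Table 1, as do its other three rows (117/130, 250/278, 652/725). No power figure is stated for any binary secondary outcome.

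**2. Inputs for the check.**

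- From the article: 329 analysed per arm, 1:1 allocation, two-sided 5%.
- Assumed: phi between a binary item at baseline and at follow-up (0 to about 0.65), and the rates. The 35% vs 25% pair is borrowed from the primary outcome; 60% vs 50% is a second illustration. Baseline prevalence equals the control rate.

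**3. Method.** Two correlated normal variables were dichotomised to give baseline and one follow-up response. Follow-up was regressed on arm by logistic regression, without and with the baseline value, in 1,500 simulated trials per setting. The cross-check is the two-proportion power formula at n/(1 − phi²). Monte Carlo standard error is about √(0.8·0.2/1500) = 0.010. Phi is shown rounded.

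| Follow-up rates | phi | Power without baseline | Power with baseline | Gain (points) | Cross-check, with baseline |
|---|---|---|---|---|---|
| 35% vs 25% | 0 | 0.799 | 0.801 | 0.2 | 0.801 |
| | 0.18 | 0.801 | 0.815 | 1.4 | 0.813 |
| | 0.31 | 0.795 | 0.831 | 3.6 | 0.839 |
| | 0.47 | 0.804 | 0.887 | 8.3 | 0.888 |
| | 0.63 | 0.788 | 0.957 | 16.9 | 0.950 |
| 60% vs 50% | 0 | 0.722 | 0.725 | 0.3 | 0.733 |
| | 0.19 | 0.720 | 0.751 | 3.1 | 0.749 |
| | 0.33 | 0.715 | 0.761 | 4.6 | 0.781 |
| | 0.50 | 0.739 | 0.856 | 11.7 | 0.845 |
| | 0.65 | 0.709 | 0.905 | 19.6 | 0.923 |

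**4. Chance imbalance.** The true marginal log odds ratios are ln[(0.35/0.65)/(0.25/0.75)] = 0.48 and ln[(0.6/0.4)/(0.5/0.5)] = 0.41. For phi from about 0.2 to 0.65, a 5-point baseline difference moves the unadjusted estimate by 0.03 to 0.16 in the first setting and 0.04 to 0.13 in the second. After adjustment the shift is at most about 0.02. A 5-point difference is not rare: the standard error of the baseline difference is √(2·0.25·0.75/329) = 0.034 or √(2·0.5·0.5/329) = 0.039, so 5 points is about 1.5 or 1.3 standard errors.

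**5. Change of estimand.** Entering baseline as a covariate makes the odds ratio conditional. At phi 0.47 the mean log odds ratio goes from 0.49 to 0.63. That reflects the scale of the odds ratio; the intervention effect itself has not grown.

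**The case against.** The strongest reply has four parts.

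- **No affected outcome is named.** The secondary outcomes are mostly scales, and any analysed as continuous already use baseline. The one plainly binary item in the list, detection of polyps or cancers, has no baseline counterpart among the repeated questionnaire measures. This stands. A reader might infer that the second hypothesis (risk perception and intentions) rests on these binary models, but the article never says those measures are dichotomised.
- **The GEE sentence is condensed, and repeated measures could include baseline as a response.** The text does not state this, and the reading does not rescue the model. No time term, arm-by-time term or equal-baseline constraint is given. If one arm coefficient were fitted across all four waves with a constant effect δ after baseline, it would average roughly (0 + δ + δ + δ)/4 = 0.75δ. Nor is the matter simply left to the SAP: the article names covariates for each model and says where baseline adjustment applies.
- **The sensitivity analysis covers imbalance.** Its list is open-ended, so it could include the baseline outcome. It does not name it, and it leaves the main analysis unchanged.
- **The numbers rest on assumptions.** This stands. Phi and the secondary rates are not in the article, and the simulation uses a single wave without general practice, not the full repeated-measures GEE.

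A reader might also infer that the planned estimates are biased or the tests invalid. They are not: under randomisation the unadjusted comparison is valid on average, and imbalance matters only conditionally on the sample drawn.

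**Conclusion.** The point holds as one of efficiency and consistency. The stated binary model omits a covariate that is already measured and that the protocol's own reasoning supports. With 329 per arm the cost is about 0 power points at phi 0, 1 to 5 at 0.2 to 0.3 and 8 to 12 at about 0.5; the larger losses near 0.65 need a correlation that nothing in the article establishes. All these sizes are illustrative, resting on assumed correlations, assumed rates and one follow-up wave. How many endpoints are affected cannot be told from the article. The primary analysis, the sample size and the type I error rate are untouched.

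**What to change.** Before unblinding, list the repeated secondary endpoints that will be analysed as binary. For each one with a baseline counterpart, include the baseline value in the GEE together with arm-by-time terms for 1, 6 and 12 months. Either form is acceptable:

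- **As a covariate.** State that the odds ratio is conditional on baseline, and report a standardised risk difference beside it.
- **As a fourth time point with arms constrained equal at baseline**, matching the continuous model. The odds ratio is then not conditional on the baseline response. The working correlation should not be independence, because the baseline response would then add nothing to the follow-up contrasts.

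Endpoints with no baseline counterpart, such as polyp detection, stay as planned. If the SAP already specifies this, only the description of the binary model needs to be brought into line with it.

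The cost is a few extra model terms and a sentence on the estimand. No new data, no larger sample and no change to trial conduct are needed.
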